### Sample Size

The sample size calculation is based on the primary outcome measure (change in TRF score between T2 and T3) which is hierarchically ranked on top of the multiple testing procedure. Based on the results described above (14, 15, 64), it is assumed that the standardized treatment effect for this outcome expressed by Cohen's d amounts to d = 0.25. With a two-sided significance level of α = 0.05 and a power of 1–β = 0.8 using a two-sample *t*-test, 253 patients per group (*n* = 506 in total) are required. Since the primary outcome is measured on the child level and it is possible to enroll multiple children per patient, a hierarchical multi-level model with patients at level 1 and children at level 2 will be fitted. Taking a drop-out rate of 20 % into account, *n* = 634 patients need to be enrolled into the trial in the analysis. This attrition rate is conservative and based on results from the longitudinal STAR^*^D study that also carried out long-term follow-up assessments (13), as well as on other studies in the field that report even lower attrition rates (65, 66). The problem of attrition and missing values will also be addressed in the analysis by applying the intention-to-treat principle. For missing values, imputation techniques will be applied, thus partly resolving this problem. Since it is assumed that parts of the outcome variance can be explained by the inclusion of covariates, the actual power of the analysis by a linear multi-level model is expected to be higher than 1–β = 0.8. Assuming that the number of children enrolled per patient amounts to 1.5, we expect that *n* = 950 children will participate in the trial. The enrollment of more than one child per patient is expected to yield an additionally increased power. Sample size calculation was performed using SAS v9.4 (SAS Institute, Cary, NC).

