### Randomization

Patients will be assigned in a 1:1 ratio to either the control intervention (CBT) or the experimental intervention (CBT+Triple P) through a centralized web-based tool (www.randomizer.at). Randomization will be performed stratified by center, comorbidity (yes/no), and total number of children (1/more than 1). To achieve equal group sizes per stratum block randomization will be performed. The block length will be defined by the study biometrician and treated confidentially to prevent selection bias.

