Data missing for the primary outcome variable will be replaced by using multiple imputation (68) which takes the covariates treatment group, center, number of comorbidities, number of children, baseline TRF score at T2, and length of waiting period between T1 and T2 (in weeks) into account by applying the fully conditional specification method (69). This will be realized using the option “FCS” of the SAS “MI” procedure implemented in SAS 9.4. Sensitivity analyses will be performed by applying alternative methods dealing with missing data such as complete case analysis. All secondary outcomes will be evaluated descriptively, and descriptive *p*-values are reported together with 95% confidence intervals for the corresponding effects. Further exploratory analyses will be performed to identify potential prognostic factors (e.g., parental disorder, child psychopathology, socio-economic status) and mediators (e.g., Brief Symptom Inventory/BSI, Parenting Questionnaire/EFB, Parental Stress Inventory/ESF) for an intervention effect. The safety analysis includes calculation of frequencies and rates of adverse and serious adverse events together with 95% confidence intervals. All analyses will be performed with SAS version 9.4 or higher.

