### Pre-assessment T1 and Assessment of Eligibility

After an initial screening of eligibility for an as early and effective as possible selection of patients and their families and a regular intake consultation with the patient in the outpatient clinic, the patients and their families (children over the age of 6 years) are invited to an informational session at the study center. During this session, the families are informed about the study procedure before signing their consent to participate in the study. For pseudonymized data collection, each participant is assigned a Screening-ID. To assess a broad range of DSM-5 based psychological disorders and comorbid ones as well as severity ratings, structured clinical interviews for patients (DIPS), and children (Kinder-DIPS parent version or SIVA) are conducted with the patient respectively a parent (for each child separately). The parent, with whom the Kinder-DIPS/SIVA is conducted, has to be the same for all children of a family at all measurement points. The in- and exclusion criteria are checked on the basis of the information collected during the screening and the diagnoses based on the clinical interviews. Feedback to diagnoses is given in a separate session. If a patient and its family fulfill all the in- and none of the exclusion criteria, the family is included in the trial and records for the eCRF are created for all the included family members. The family is invited to another session in which interviews about knowledge about mental disorders are conducted with each included family member. After this session codes are handed out with which the family members can log into REDCap at home to complete the questionnaires. Forms with REDCap-codes for the children's caregivers or teachers (one caregiver/teacher for each included child) are also handed out to the family with the request to forward them to the respective caregiver/teachers. There is no reference to the clinical trial of the COMPARE-family project on the caregiver/teacher's form; rather, the questionnaire is generally presented as part of a study at the department of psychology the UMR. After the final inclusion in the study, the randomization to one of the two treatment arms (CBT or CBT+Triple P) takes place. If needed, further probatory sessions can take place at the study centers. In a separate feedback session, the patient is informed about the treatment condition and results of the diagnostic process.

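### The stated imputation model contains nothing beyond the primary model's own terms, so it adds little to a complete-case analysis; auxiliary variables already collected would strengthen it

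*Protocol article*

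**What the plan says.** The Statistical Methods section of the protocol article specifies the imputation by method, software and covariates. The method is fully conditional specification (FCS) in the SAS MI procedure, and the covariates begin: "Data missing for the primary outcome variable will be replaced by using multiple imputation (68) which takes the covariates treatment group, center". The rest of the list is number of comorbidities, number of children, T2 TRF and weeks of waiting between T1 and T2.

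The same section tests treatment in a linear mixed model of children within patients. That model adjusts for center, number of comorbidities, number of children, T2 TRF and waiting time.

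On robustness it says: "Sensitivity analyses will be performed by applying alternative methods dealing with missing data such as complete case analysis". The Sample Size section says of attrition: "For missing values, imputation techniques will be applied, thus partly resolving this problem".

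At T1 the teacher forms are "handed out to the family with the request to forward them to the respective caregiver/teachers", and the sections on T2, T3 and T4 describe the same route. The T1 section also says that the patient is told the treatment condition. Table 1 lists the (C-)TRF and the parent CBCL at T1, T2, T3 and T4.

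**The concern.** Imputation helps when it brings in information that the analysis model lacks. Here the imputation list is the analysis list, so where only the follow-up score is missing there is nothing new to bring in. The imputation then corrects only for missingness that depends on arm, center, comorbidity, number of children, T2 score and waiting time.

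The way the outcome is collected makes other kinds of missingness plausible. The teacher's form does not mention the trial, which helps protect the rating itself. Whether the form reaches the teacher, however, is up to a family that knows its arm and sees how the child is doing. The electronic form does not allow items to be skipped, so missing data will mostly be whole forms. A parent may still have completed the CBCL for that visit, and the T1 teacher score or the other follow-up score may exist. The stated list uses none of these.

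Both confirmatory tests (T2 to T3, then T2 to T4) rest on this step. If return is selective in a way that the covariates do not capture, the imputed and complete-case analyses will be off by about the same amount, and their agreement could be mistaken for evidence of robustness.

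**Working it through.** **1. The plan's own figures.** Inputs from Sample Size and Randomization: an assumed Cohen's d of 0.25, a two-sided test at 5%, 80% power, a t-test for two groups, and equal allocation. The noncentral t distribution gives 253 per arm (power 0.801), matching "253 patients per group". With 20% dropout, 253/0.8 = 316.25, rounded up to 317 per arm, or 634 in total. 634 × 1.5 = 951 children, against 950 stated. The sample size reproduces and is not in question.

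**2. The two lists side by side.**
- Analysis: treatment (tested), center, comorbidities, number of children, T2 TRF, waiting time.
- Imputation: treatment, center, comorbidities, number of children, T2 TRF, waiting time.
- Collected but not listed for imputation: T1 TRF, the other follow-up TRF, parent CBCL at T1 to T4, and BSI, EFB and ESF.
- No family term is named.

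**3. Why equal lists add almost nothing.** Let X be the common design matrix, with o for observed and m for missing outcomes. The imputed outcomes centre on X_m β̂_o, where β̂_o is the complete-case least-squares fit. Averaged over many imputations, least squares on the completed data gives

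(X′X)⁻¹(X_o′X_o β̂_o + X_m′X_m β̂_o) = β̂_o,

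because X′X = X_o′X_o + X_m′X_m. A mixed model weights siblings differently from least squares and the number of imputations is finite, so the match is close and not exact.

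**4. Simulation with only the follow-up score missing.** Assumptions not in the article: half the 634 families have one child and half have two; missingness depends on baseline and arm; imputation is run with one row per child; 20 imputations; 300 replicates. True effect −0.25.

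| Sibling ICC, missing | Complete case | Stated MI | Correlation | SE complete case | SE MI | SE ratio | ICC after MI |
|---|---|---|---|---|---|---|---|
| 0, 20% by family | −0.2485 | −0.2489 | 0.995 | 0.0740 | 0.0740 | 1.00 | 0.02 |
| 0.3, 20% by family | −0.2500 | −0.2498 | 0.994 | 0.0795 | 0.0781 | 0.98 | 0.23 |
| 0.5, 20% by family | −0.2476 | −0.2485 | 0.991 | 0.0828 | 0.0801 | 0.97 | 0.38 |
| 0.3, 35% by family | −0.2500 | −0.2498 | 0.989 | 0.0880 | 0.0852 | 0.97 | 0.18 |
| 0.3, 20% by child | −0.2511 | −0.2513 | 0.992 | 0.0781 | 0.0769 | 0.98 | 0.19 |

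Coverage of the two methods was within 1 percentage point in every row.

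A second simulation (ICC 0.4, retest correlation 0.6, about 30% missing completely at random, 10 imputations, 1500 replicates) gave a correlation of 0.978. The fitted ICC was 0.39 without imputation and 0.19 after it, and the model SE was 0.94 to 0.98 of the empirical SE.

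**5. Selective return, for illustration only.**
- *Milder mechanism:* forms returned less often in the control arm when parent CBCL is high. At CBCL–TRF correlations of 0.3 and 0.5, the bias was 0.045 and 0.072 SD for complete case and 0.047 and 0.076 SD for the stated MI. The latter are 0.047/0.25 = 19% and 0.076/0.25 = 30% of d. With T1 TRF and CBCL added, the bias was 0.001 and −0.001.
- *Deliberately strong mechanism:* missingness related to a post-baseline score in opposite directions in the two arms (ICC 0.3, 20% missing). True effect −0.25; complete case −0.394 (coverage 0.56); stated MI −0.391 (coverage 0.54); MI with that score added −0.257 (coverage 0.96).

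In both cases the stated MI and complete case were wrong by about the same amount.

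**The case against.** A reader might draw stronger conclusions, and the document does not support them.

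- **That the two analyses must agree, making the sensitivity analysis empty.** Step 3 applies when only the follow-up score is missing. The T2 form takes the same route through the family, so T2 scores will be missing too. If FCS imputes them, MI keeps children whom complete case drops, and the results can differ. The sensitivity sentence is also open-ended: it names complete case as an example and excludes nothing. Not naming a further method is the kind of detail left to the analysis plan.
- **That the SAS procedure discards sibling correlation.** The article does not state the data layout. One row per family is possible in the same procedure and would keep the correlation. Even with one row per child, the SE falls by only about 2 to 6%. A nominal 5% test then runs at about 5.5% (critical value 1.96 × 0.98) to 6.5% (1.96 × 0.94). The fall in the ICC looks dramatic, but the ICC is not the estimand.
- **That a bias of 19 to 30% of d is to be expected.** The article gives no evidence for the assumed arm-specific mechanism or its strength, and about 30% missing exceeds the planned 20% dropout. The near-perfect repair is partly circular, because missingness was generated from a variable then added to the imputation. If return depends on the unseen teacher score itself, auxiliaries repair it only in part.
- **That the claim of partly resolving attrition is false.** It is modest, and it holds for missingness explained by the listed covariates.

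One further limit stands: at T3 and T4 the parents' codes and the teacher forms are handed out at the same session, so a family that has left the study will usually lack both.

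The match between the two lists remains. The article fixes that list explicitly, so it is a stated choice and not an omission.

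**Conclusion.** The point holds in limited form. The stated imputation uses only treatment and the primary model's covariates. Where only the follow-up (C-)TRF is missing, it gives nearly the complete-case result (correlation 0.98 to 0.995) and corrects only for missingness related to those covariates. Complete case is therefore a weak check on it.

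The near-equality follows from the algebra and was seen at every ICC and missing rate tried. The size of any bias cannot be taken from the document: the illustrations run from 0.047 to about 0.14 SD (0.391 − 0.25 = 0.141) and depend wholly on the assumed return mechanism. Loss of sibling correlation is a secondary point, conditional on one row per child.

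This is a worthwhile and inexpensive improvement, not a must-fix error.

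**What to change.** 1. Add to the FCS model the T1 (C-)TRF, the T3 score when imputing T4 and the reverse, and parent CBCL at T1 to T4 where available.
2. State the data layout. If one row per child was intended, use one row per family (each child's scores as separate variables) or a two-level imputation, so that sibling correlation is kept.
3. Keep complete case and supplement it with a delta-adjusted analysis in which the shift applied to imputed scores varies by arm.

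The cost is wording and programming before database lock, since every variable is already collected. The imputation model becomes somewhat larger. The repair is partial, because the concurrent CBCL will often be missing for families that drop out entirely; for them the T1 and T2 measures and any earlier follow-up score carry the added information.

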### Data management, monitoring, and quality assurance

#### Training of Study Personal and Treatment Fidelity

All study personal (assessors, therapists, and supervisors) will be trained before taking part in the study. As all sites are part of associated university training institutes that conform to the highest psychotherapeutic standards. All therapists will receive intense training in CBT for the different disorders. The Triple P institute in Münster, which is the official and certified Triple P institution in Germany, will carry out Triple P training. Trained and certified supervisors will supervise every fourth treatment session at the study sites. At each participating center, a clinical project manager is responsible that the study is conducted in accordance to the procedures outlined in the study protocol. Concerning all information and data collected during the study, all study personal maintain professional secrecy and confidentiality.

After each treatment session, the therapists indicate CBT adherence by rating a checklist extracted from the disorder specific therapy manuals as outlined in the proceedings in psychotherapy (33). Upon termination of a study therapy, a supervisor rates the overall adherence of the therapy based on the adherence checks completed after every session. The adherence rate is documented in the eCRF for further analyzes.

Treatment fidelity/integrity will be analyzed with rating schemes for 5% randomly selected videotaped treatment sessions by the study coordination at the UMR. Before the videotapes are rated; they will be checked for any cues/hints potentially indicating the treatment condition; those will be erased.

#### Data Collection and Retention

For each included family, a study file will be created at the study site in which all local study documents will be archived. An electronic case report form (eCRF) will be used for the data collection using the secure web based electronic data capture (EDC) tool REDCap (77). The participants complete most of the questionnaires directly in the eCRF. A study staff at each site creates log-in-codes that are handed out to the participants during on site sessions with which the participants (parents, children over the age of 8 years and caregivers/teachers) can log into REDCap to complete the questionnaires at home. The families are asked to fill out the forms independently. The eCRF is programmed to not allow skipping answers to prevent missing data. If questions occur, filling out the eCRF can be paused and continued later on with a trained assessor at a study site. A study staff will enter locally collected data into REDCap preferably on the day of data collection. Upon termination of the study, all local study documents at the study sites will be sent to the UMR where the documents will be digitalized. For supervision and to ensure treatment fidelity, all study sessions will be videotaped. The video data will be stored in encrypted form using VeraCrypt which is useable free of cost under the Apache License 2.0. All videotapes will be send to the study coordination at the UMR and stored there. Upon termination of the study, all video data will be destroyed.

All local study documents are part of the Investigator Site File (ISF) as outlined in section 8 of the ICH Consolidated Guideline which is stored and archived according to the legal retention period. Data quality assessment of the eCRF will be done continuously by the Institute of Medical Biometry and Informatics Heidelberg during the study. Any entry and correction in the EDC system will be documented automatically in an audit file. Completeness, validity, and plausibility of data will be checked in time of data entry (edit-checks) and using validating programs which will generate queries. All assessments and modifications are immediately accessible via web access. The clinical project manager at each study site is also responsible for online transmission of data and site-specific quality assurance. Upon completion of the study, all data will be exported into different data formats for further analyses. The primary data will be made accessible to the public for re- and meta-analyses through PsychData at the Leibniz Institute for Psychology Information (https://www.psychdata.de/). All data will be used in accordance to data protection regulations and the data safety guidelines of the German Psychological Society (DGPs).

#### Ethical and Legal Aspects

Working with a highly vulnerable group, the procedures set out in this study protocol are designed to ensure that the investigators abide by the principles of the Good Clinical Practice (GCP) guidelines of the International Conference on Harmonization (ICH) and the Declaration of Helsinki and its later supplements. The study will be carried out adhering to local legal requirements. The lead ethics committee at the department of psychology at the UMR has approved the study procedure, study information, and informed consent forms in December 2017 and its subsequent amendments in May and July 2018. A positive ethics committee vote is required at a study site (ethics committees at the departments of psychology at Bielefeld University, Ruhr-University Bochum, Justus Liebig University Giessen, University of Koblenz-Landau, University of Leipzig, Johannes Gutenberg University Mainz, and Ludwig-Maximilians-University Munich), before the inclusion of a first patient at the respective site. At the beginning of the study, patients and their families are informed verbally and written about the aims of the study and the study procedures. All patients and their families (children over 6 years of age) need to provide written informed consent for study participation. For children to participate in the study, written informed consent by all legal guardians is required. Every participant can drop out of the study at any time. All dropouts will be documented in the eCRF.

#### Pseudonymization

After signing the informed consent, each study participant is assigned a pseudonymized screening-ID. The screening-ID consists of three parts: specific number for the study site, consecutive screening number and individual coding number (1 = patient, 2 = partner, 3, 4, 5 = included children in order of increasing age, X = ex-partner). Members of a family can be recognized by the first two parts of the screening-ID (specific study site number and consecutive screening number).

There is a coding list on paper at each study site on which names and screening-IDs are documented. The coding lists, which are kept locked away, are accessible only to study personal. The lists will be destroyed upon termination of the study but no later than 2021/12/31. After that, all data will be fully anonymized. As long as the coding lists exist, participants can request the deletion, respectively the destruction of all their collected data.

#### Clinical Monitor

A clinical monitor is responsible for overviewing the implementation of the study in accordance to the ICH-GSP guidelines at the study sites. The clinical monitoring includes pre-study, initiation, intermediate and close-out visits to the study sites. During the site visits, the clinical monitor examines the protocol adherent study implementation, the safety of the patients and the data consistency (e.g., comparison of local study documents and eCRF records).

#### Data Safety Monitoring Board

An independent Data Safety Monitoring Board (DSMB), consisting of a university professor, which is an expert in the field of the study, and a biometrician, is responsible for monitoring the study as well as assessing the study protocol adherence and the study progress (especially the recruiting plan). The DSMB will be informed about all safety aspects of the study (especially serious adverse events, SAE) and will review them regularly. If necessary, the DSMB will recommend changes to the study protocol or the termination of the study.

### Dissemination

The results of this study will be made available to the larger scientific community via peer-reviewed publications in open access scientific journals. Politicians, public health services and stakeholders will be informed through the COMPARE website, conferences, teaching seminars, flyers, newsletters, and personal contacts throughout the study and beyond, thus improving public policy and health care decisions concerning preventive interventions and treatments for COPMI. As all study sites are university based outpatient clinics the implementation of results in ongoing and future practice is ensured.

Upon termination of the study, all primary data will be made available to the scientific community in a completely anonymized manner for re- and meta-analyses using PsychData, a data-sharing platform developed by the Leibniz Institute for Psychology Information (ZPID, https://www.psychdata.de).

